#### Inclusion criteria

Willing and able to give informed consent for participation in the trial (or with personal legal representative consent)Willing and able to report any safety concerns or with a suitable carer able to report these if unableRegistered at either a practice using electronic health record systems (e.g. EMIS or SystmOne) or contributing to or willing to contribute to The Oxford Clinical Informatics Digital Hub ORCHID [18].Aged 75 years or above at recruitment.Controlled systolic blood pressure, defined (in accordance with NICE 2019 guidelines) [9] as less than 140 mmHg (if aged 75–79 years) or less than 150 mmHg (if aged 80 years or above). Systolic blood pressure level will be based on screening measurements taken at baseline (mean of the 2nd and 3rd readings taken in a standardised manner) [19] or from patient records if a face-to-face baseline visit is not possible.Prescribed two or more antihypertensive medications for at least 12 months prior to trial entry. Antihypertensive medications defined as any ACE inhibitor, angiotensin II receptor blocker, calcium channel blocker, thiazide and thiazide-like diuretic (including loop diuretics), potassium-sparing diuretic, alpha-blocker, beta-blocker, vasodilator antihypertensives, centrally acting antihypertensives, direct renin inhibitors, adrenergic neurone blocking drugs.Stable dose of antihypertensive medications for at least 4 weeks prior to trial entry.Moderate or severe frailty (defined by an eFI score ≥ 0.20) [20] and/or high risk (> 5%) of hypotension, syncope or falls in the next 5 years, based on STRATIFY risk prediction algorithms [21, 22] applied to an individual’s electronic health record.

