### Baseline assessments

After consent, participants undergo baseline procedures with a research nurse, or other appropriately trained and delegated member of the team, including measurement of clinic blood pressure readings. Blood pressure is taken after participants have been seated for 5 min of rest using a clinically validated blood pressure monitor, and the mean of the 2nd and 3rd readings is used the define trial eligibility. To test for orthostatic hypotension, two further readings are taken in the standing position, immediately, and after 3 min [23]. Once eligibility is confirmed, the participant then completes the trial questionnaires including the Illness Perception Questionnaire (symptom list) [24], Multimorbidity Treatment Burden Questionnaire [25], Katz Activities of Daily Living (ADL) - Life Ability Questionnaire [17], and Beliefs about Medicines Questionnaire (BMQ) General [15] and the EQ-5D-5L [16] which will give an interpretation of quality of life. Also included is an adapted variant of the Client Service Receipt Inventory [26] to measure health economic burden, the Free-Cog [27] to assess cognition, and the Attitudes Towards Deprescribing Questionnaire [28] to determine patient perception of medication reduction. Once these questionnaires have been completed to the best of their ability, they are then randomised into the trial by the person performing the baseline procedures. Stratified randomisation is used to individually allocate participants (1:1) to one of the two trial groups using a fully validated web-based randomisation system (Sortition) with stratification factors age (i.e. 75–79 and ≥ 80 years) and region of England. Randomly permuted block sizes is used within strata.

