### Statistical methods for primary and secondary outcomes

The primary analysis will be according to randomised treatment assignment and will include all randomised participants for whom data are available, as defined by protocol eligibility criteria. Deprescribing antihypertensive medication will be deemed non-inferior to usual care in terms of death or emergency hospital admission if the lower limit of a 95% confidence interval for the absolute risk difference between usual care and medication reduction groups is above − 5%, i.e. if the percentage of emergency hospitalisations/deaths in the deprescribing group is less than 5 percentage units higher than in the usual care group. This primary outcome will be analysed using a generalised linear mixed effects model. The response will be a binary indicator of whether the participant experienced death or emergency hospitalisation at 1 year. The model will include age and NHS England region as fixed effects and site as a random effect. Any covariates found to be predictive of missingness in the outcome, through fitting univariate logistic regression models, will be included in the model.

Generalised linear models adjusting for age as a fixed effect and site as a random effect will be used for secondary outcomes e.g. differences in the proportions of patients with serious falls, serious hypotension, syncope, fracture, hospitalisation/death, any non-serious adverse event, ADWE, all-cause death, major cardiovascular events, stroke, MI and perceived side effects to antihypertensive at 12 months, differences in mean change in treatment burden score, number of prescribed medications, number of prescribed antihypertensives, blood pressure, quality of life at 12 months.

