### Health economic evaluation

The health economic evaluation aims to provide evidence on whether or not deprescribing of antihypertensives is cost-effective. Two forms of economic evaluation will be conducted: (i) a within-trial economic evaluation of deprescribing that mirrors the time horizon of the non-inferiority trial; and (ii) a decision-analytic modelling-based economic evaluation that will extend over a lifetime horizon. The economic assessment methods will adhere to the recommendations of the National Institute for Health and Care Excellence (NICE) Reference Case [33]. 

The within-trial economic evaluation will be conducted from the recommended NHS and personal social services perspective [33]. Primary research will be undertaken to estimate the cost of implementing deprescribing, including the costs associated with patient identification, monitoring activities and any follow-up/management. Broader resource utilisation is captured through two principal sources: (i) the electronic primary care health records and linked Hospital Episode Statistics; and (ii) Client Service Receipt Inventory questionnaires completed as described above at follow-up. Unit costs for resource inputs will largely be derived from national reference tariffs. Responses to participant EQ-5D-5L questionnaires completed at baseline and 12 months post-randomisation will be converted into health utilities using established utility algorithms for the purposes of quality-adjusted life year (QALY) estimation, with QALY profiles estimated using the trapezoid rule. Bivariate regression of costs and QALYs, with multiple imputation of missing data, will be conducted to generate within-trial estimates of incremental cost-effectiveness associated with deprescribing. Sensitivity analyses will be undertaken to assess the impact of areas of uncertainty surrounding components of the economic evaluation.

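### Continuous secondary outcomes are modelled as mean change adjusted for age and site, without the outcome's own baseline value, which gives up some precision at no saving

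*Protocol article*

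**What the plan says.** The section on statistical methods for primary and secondary outcomes gives one model statement for all secondary outcomes: "Generalised linear models adjusting for age as a fixed effect and site as a random effect will be used for secondary outcomes". Its examples run from binary events to five continuous or count measures, the latter described as "differences in mean change in treatment burden score, number of prescribed medications, number of prescribed antihypertensives, blood pressure, quality of life at 12 months". The baseline value of the measure is not listed as a covariate, and no other section adds it. Region, which is in the primary model, is not listed either.

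On what is available at baseline:
- **Blood pressure:** the Baseline assessments section has procedures "including measurement of clinic blood pressure readings".
- **Treatment burden:** the same section places the treatment burden questionnaire before randomisation.
- **Quality of life:** the same section places EQ-5D-5L before randomisation, and the Health economic evaluation section refers to "Responses to participant EQ-5D-5L questionnaires completed at baseline and 12 months post-randomisation".
- **Drug counts:** no baseline count is listed as a measurement. Eligibility requires "Prescribed two or more antihypertensive medications for at least 12 months prior to trial entry", and prescribing data come from electronic health records, so a baseline count should be obtainable. That is an inference.

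The Trial outcomes section describes treatment burden, medication burden and blood pressure as differences in averages, not in change.

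**The concern.** A change score already needs the baseline value for every participant analysed. Subtracting it fixes its coefficient at 1. Using it as a covariate lets the data choose the coefficient, which cannot raise the residual variance beyond one degree of freedom, negligible at this sample size. The stated model therefore collects the baseline and then uses it less well than it could.

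At stake is the width of the intervals for blood pressure, quality of life and treatment burden. The predecessor trial, as summarised in the Background, saw a systolic rise of only 3 mmHg, so modest differences matter here. Naming baseline adjustment in advance also guards an open-label trial against later argument over chance baseline differences. The article states the target both as a difference in averages and as a difference in mean change; a linear model that includes baseline gives the same treatment estimate for either.

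**Working it through.** **Inputs.** From the article: 3,014 randomised 1:1 and a 5% loss allowance, hence 1,507 × 0.95 ≈ 1,432 per arm. Not in the article, so assumed: the correlation r between baseline and 12-month values (strictly, after adjusting for age and site) and the SDs at the two times.

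**The plan's own figure.** The article gives none for the continuous outcomes. The sample size for the primary outcome does reproduce: 20.7% plus 1 point is 21.7% in both arms, which with a 5-point margin, one-sided 2.5% and 90% power gives 1,429 per arm, 1,505 after 5% loss, and 3,010 in total against 3,014 stated.

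**General result.** With baseline SD s0, follow-up SD s1 and correlation r, taken as common to both arms:
- change score: s0² + s1² − 2r·s0·s1
- baseline-adjusted: s1²(1 − r²)
- difference: (s0 − r·s1)², which is never negative.

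No equality of SDs is needed for the direction.

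**Size with equal SDs.** The variances become 2(1 − r) and 1 − r² in units of s², so the ratio is 2/(1 + r). The smallest difference detectable with 90% power at two-sided 5% is (1.960 + 1.282) × √(2V/1,432), in SD units.

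| Assumed r | Variance ratio | Interval wider by | Detectable, change score | Detectable, adjusted |
|---|---|---|---|---|
| 0.3 | 1.54 | 24% | 0.143 SD | 0.116 SD |
| 0.5 | 1.33 | 15% | 0.121 SD | 0.105 SD |
| 0.7 | 1.18 | 8% | 0.094 SD | 0.087 SD |

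At r = 0.9 the ratio is 1.05. A simulation of 2,000 trials at each of the three values gave adjusted-to-unadjusted variance ratios of 0.66, 0.77 and 0.83, against 0.65, 0.75 and 0.85 by formula.

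**Blood pressure.** Eligibility caps the baseline systolic reading at 140 or 150 mmHg by age, so s0 falls below s1 and the table does not apply. Assume an SD of 15 and a mean of 138 before selection, and one cut at 145 standing in for the two limits.
1. The standardised cut is a = (145 − 138)/15 = 0.467. With λ = φ(a)/Φ(a) = 0.526, the share of baseline variance left is k = 1 − aλ − λ² = 0.477, so s0 is about 10.4.
2. Under a linear relation, selection on baseline leaves the slope of follow-up on baseline unchanged. With r now the correlation before selection, the ratio becomes 1 + k(1 − r)/(1 + r).
3. This gives 1.26 at r = 0.3, 1.16 at 0.5, 1.12 at 0.6 and 1.08 at 0.7. Intervals are about 12%, 8%, 6% and 4% wider.

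**Change score against ignoring baseline.** The variance difference is Var(Y − X) − Var(Y) = s0²(1 − 2b), where b is the slope, so the threshold is b = 0.5 and not r = 0.5 once the SDs differ. At r = 0.6 before selection, the correlation after selection is 0.46, yet the change score has 0.88 of the follow-up-only variance.

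**The case against.** The strongest reply is that the sentence is shared by about a dozen binary outcomes and five continuous ones. A baseline value means nothing for death or stroke, so a common covariate list would naturally omit it. The sentence does not say that age and site are the only covariates, and a model of change with baseline added would still be described as a comparison of mean change. The full analysis plan is not shown and may include it. This lowers confidence that the final analysis will be deficient. It does not change what the article states: a response and a covariate set, with baseline absent.

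The loss is also modest. Even unadjusted, the detectable differences in the table are 0.09 to 0.14 SD. That stands.

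Two stronger readings should not be drawn.
- **Truncation.** A reader might infer that the blood pressure limit pushes the correlation below 0.5 and so makes the change score worse than ignoring baseline. That rule requires equal SDs, which truncation removes. The slope decides, and truncation leaves it alone; the narrower baseline also shrinks the penalty. Applying 2/(1 + r) to the truncated correlation of 0.46 would give 1.37, where the ratio is 1.12.
- **QALYs.** A reader might infer that the economic analysis omits baseline utility. The article says only "Bivariate regression of costs and QALYs, with multiple imputation of missing data, will be conducted", and names no covariates of any kind. In a condensed article that silence is not a defect; it is a point to confirm in the full plan.

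**Conclusion.** The point holds as one of precision, confined to the continuous secondary outcomes. The stated model is never more precise than one with baseline as a covariate. Under equal SDs its intervals are about 8% to 24% wider for r between 0.7 and 0.3. For blood pressure the figure is about 4% to 12% under the assumed distribution. The correlations, the SDs and the blood pressure mean are assumptions, so these are ranges. For the two drug counts, the availability of a baseline is inferred, and the equal-SD figures are only a rough guide.

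A reader might go further and call the planned comparisons biased or the trial underpowered. The article does not support that. Under randomisation the change-score comparison is unbiased on average; what is lost is precision and some protection against chance imbalance. The primary outcome, its margin and the sample size are not touched.

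**What to change.** State that each continuous secondary outcome will be analysed as the 12-month value (or the change) with the baseline value of the same measure as a covariate, plus treatment, age and region as fixed effects and site as a random effect. Region belongs there because randomisation is stratified by it and the primary model already includes it. Say where the baseline drug counts come from, and give a rule for missing baseline values. If the full analysis plan already specifies this, bring the article's wording into line with it, and confirm there whether baseline utility enters the QALY equation.

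The cost is a change of wording before analysis. No extra measurements are needed for blood pressure, treatment burden or quality of life; the drug counts need only the baseline prescribing record that a change score already requires.

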### Health economic evaluation

The health economic evaluation aims to provide evidence on whether or not deprescribing of antihypertensives is cost-effective. Two forms of economic evaluation will be conducted: (i) a within-trial economic evaluation of deprescribing that mirrors the time horizon of the non-inferiority trial; and (ii) a decision-analytic modelling-based economic evaluation that will extend over a lifetime horizon. The economic assessment methods will adhere to the recommendations of the National Institute for Health and Care Excellence (NICE) Reference Case [33]. 

The within-trial economic evaluation will be conducted from the recommended NHS and personal social services perspective [33]. Primary research will be undertaken to estimate the cost of implementing deprescribing, including the costs associated with patient identification, monitoring activities and any follow-up/management. Broader resource utilisation is captured through two principal sources: (i) the electronic primary care health records and linked Hospital Episode Statistics; and (ii) Client Service Receipt Inventory questionnaires completed as described above at follow-up. Unit costs for resource inputs will largely be derived from national reference tariffs. Responses to participant EQ-5D-5L questionnaires completed at baseline and 12 months post-randomisation will be converted into health utilities using established utility algorithms for the purposes of quality-adjusted life year (QALY) estimation, with QALY profiles estimated using the trapezoid rule. Bivariate regression of costs and QALYs, with multiple imputation of missing data, will be conducted to generate within-trial estimates of incremental cost-effectiveness associated with deprescribing. Sensitivity analyses will be undertaken to assess the impact of areas of uncertainty surrounding components of the economic evaluation.

Decision-analytic modelling will be used to extrapolate the impact of deprescribing antihypertensives beyond the follow-up period of the main quantitative evaluation. The team will adapt the model used in the original OPTiMISE study [35] to estimate the impact of deprescribing on lifetime costs and QALYs, with cost-effectiveness expressed in terms of incremental cost per QALY gained. Multi-parameter uncertainty in the model will be addressed using probabilistic sensitivity analysis [36]. Sensitivity analyses will also examine the minimal level of adverse event risk required at baseline for deprescribing to be accepted as a cost-effective strategy.

## Discussion

Current clinical guidelines suggest that doctors take into account an individual’s frailty and multimorbidity when prescribing antihypertensive treatment in older adults [37] and consider the potential for medication withdrawal where blood pressure is low and frailty is high [38]. Currently, these recommendations are not evidence-based, with very few studies examining the effects of antihypertensive deprescribing in older people having been undertaken.

A recent Cochrane review found just six trials of antihypertensive deprescribing in patients aged 50 years or older (including 1073 participants) with a maximum follow-up of 56 weeks [39]. This review found no evidence of an effect of antihypertensive deprescribing on clinical outcomes; however, very few of the trials included in this review reported outcome events of interest, and therefore, it was underpowered to show any association with hospitalisation (19 events), mortality (18 events) or cardiovascular disease (3 events).

There are some ongoing trials, including the RETREAT-FRAIL trial, which is evaluating the long-term effects of deprescribing antihypertensive therapy in nursing home residents over the age of 80 with low blood pressure (< 130 mm Hg) treated with at least 2 antihypertensive drugs [40]. The RETREAT-FRAIL trial examines the effect of gradual reduction of antihypertensive treatment on mortality during a follow-up period of an average of 3 years. It will provide valuable information about the effects of antihypertensive deprescribing in a nursing home setting, in very frail older adults, where deprescribing may be undertaken in patients with limited life expectancy. In this setting, antihypertensive treatment may be considered at the very least futile, if not potentially harmful. However, these results may not be generalisable to older adults living independently in the community, where the balance of benefit to harm from antihypertensive treatment may be much more finely balanced. For this reason, the OPTIMISE2 trial is urgently needed to support clinical decision-making for such adults in primary care.

## Trial status

The trial is open to recruitment, having received full approvals on 18th September 2023. The first participant was randomised on 16th November 2023, and recruitment is planned to continue until at least the end of 2025. Current Protocol version 3.0 dated 19-Mar-2024. Any amendments to the protocol will be communicated to all relevant parties and trial sites.

## Dissemination policy

Results from this work will be communicated to key audiences through scientific journals, patient summaries and presentations at scientific meetings and community engagement events. Some time after the trial has finished, the results will be published on the trial website. Participants will be contacted to notify them that the results have been published and giving them the weblink to the results.

## Data Availability

Data sharing statement: Requests for sharing of de-identified individual participant data and a data dictionary defining each field in the set will be considered by the corresponding author.

## Abbreviations

ACE: Angiotensin-converting enzyme
ACEI: Angiotensin-converting enzyme inhibitors
ADR: Adverse drug reaction
AE: Adverse event
AR: Adverse reaction
ADWE: Adverse drug withdrawal event
CI: Chief Investigator
CPRD: Clinical Practice Research Datalink
CRF: Case report form
CRN: Clinical Research Network
CSR: Clinical study report
CT: Clinical trials
CTA: Clinical Trials Authorisation
CVD: Cardiovascular disease
DMEC: Data Monitoring and Ethics Committee
DSUR: Development Safety Update Report
eCRF: Electronic case report form
eFI: Electronic Frailty Index
EMIS: Egton Medical Information Systems
GCP: Good Clinical Practice
GP: General practitioner
HES: Hospital Episode Statistics
HRA: Health Research Authority
IB: Investigators Brochure
ICF: Informed Consent Form
ICH: International Conference on Harmonisation
ICMJE: International Committee of Medical Journal Editors
IMP: Investigational Medicinal Product
IRB: Independent Review Board
LVSD: Left ventricular systolic dysfunction
MHRA: Medicines and Healthcare products Regulatory Agency
mmHg: Millimetres of mercury
NHS: National Health Service
NICE: National Institute for Health and Care Excellence
NIHR: National Institute of Health Research
OPERAM: Optimizing Therapy to Prevent Avoidable Hospital Admissions in Multimorbid Older Adults
OPTiMISE: OPtimising Treatment for Mild Systolic hypertension in the Elderly
OPTIMISE2: Optimising Prescription of Treatment In older patients with Mild hypertension at Increased risk of Serious adverse Events
ORCHID: Oxford Royal College of General Practitioners Clinical Informatics Digital Hub
PI: Principal Investigator
PIL: Participant/Patient Information Leaflet
QALY: Quality-adjusted life year
QOF: Quality and Outcomes Framework
R&D: NHS Trust R&D Department
REC: Research Ethics Committee
RES: Research Ethics Service
RGEA: Research Governance, Ethics and Assurance
RSI: Reference Safety Information
SAE: Serious adverse event
SAP: Statistical analysis plan
SAR: Serious adverse reaction
SDV: Source Data Verification
SMPC: Summary of Medicinal Product Characteristics
SOP: Standard operating procedure
SSAR: Suspected serious adverse reaction
STRATIFY: STRAtifying Treatments In the multi-morbid Frail elderlY
SUSAR: Suspected unexpected serious adverse reactions
TMF: Trial Master File
TSC: Trial Steering Committee
